## Abstract

**Background**: Transcranial Direct Current Stimulation (tDCS) is reportedly a potential treatment option for chronic tinnitus. The main drawbacks of previous studies are short term follow up and focusing on the efficacy of single session tDCS. This study aims to investigate the therapeutic efficacy, adverse effects (AEs) and tolerability of repeated sessions of bilateral tDCS over auditory cortex (AC) on tinnitus symptoms

**Methods**: This will be a double-blinded randomized placebo controlled parallel trial on patients (n=90) with intractable chronic tinnitus (> 2 years) randomly divided into three groups of anodal, cathodal, and sham tDCS. In the sham treatment, after 30 sec the device will be turned OFF without informing the patients. The tDCS protocol consists of 10 sessions (daily  20 min session; 2 mA current for 5 consecutive days per week and 2 consecutive weeks) applied through 35 cm
^2^ electrodes. The primary outcome is tinnitus handicap inventory (THI) which will be assessed pre- and post-intervention and at one month follow-up. The secondary outcomes are tinnitus loudness and distress to be assessed using a visual analogue scale (VAS) pre-intervention, and immediately, one hour, one week, and one month after last stimulation. The AEs and tolerability of patients will be evaluated after each session using a customized questionnaire. Possible interactions between the disease features and treatment response will be evaluated.

**Discussion**: To our knowledge this is the first study to investigate the effects of repeated sessions of tDCS on chronic tinnitus symptoms with one month follow-up. In addition, the AEs, and tolerability of patients will be studied. In addition, the possible interactions between the disease specific features including the hearing loss, laterality, type of tinnitus, and treatment response will be evaluated.

**Trial registration**: The study has been registered as a clinical trial in Iranian Registry of Clinical Trial (
IRCT2016110124635N6) on the 01/06/2017.

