21^. The main hypothesis for therapeutic application of tDCS in tinnitus is disturbing ongoing abnormal neural activities responsible for tinnitus. According to this approach, the areas involved in the pathophysiology of tinnitus are targeted by tDCS. The other hypothesis of eliciting therapeutic outcomes from tDCS is inducing plastic changes to alter the maladaptive plasticity of the involved regions. The important point for treatment of tinnitus is that there is a large network consisting of different auditory and non-auditory regions with overlapping functions
^22–
24^.

Most of the studies performed to date, have focused on the effects of single tDCS session on tinnitus symptoms, with short term follow ups ranging some hours to some days. To our knowledge, there is no published study investigating the effect of repeated sessions of tDCS over the auditory cortex (AC) on tinnitus symptoms as well as the AEs of and tolerability to the tDCS with one month follow up. This study aims to investigate the effects of repeated sessions of tDCS on tinnitus symptoms with one month follow-up. Our main hypothesis is that repeated sessions will lead to aggregative therapeutic effects on tinnitus. In addition, we want to evaluate possible association between treatment response, and patient's and tinnitus specific characteristics including gender, THI basal score, laterality, tinnitus quality, duration, hearing loss class, etc.

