### Hearing assessment

Hearing assessments will be performed in an acoustically isolated chamber (ISO 8253–1:2010). Pure-tone audiometry will be performed using AC 40 dual channel Audiometer (Intracoustics Co., Denmark). The hearing thresholds will be recorded over the frequency ranges of 250 to 8000 Hz for air conduction and 500 to 4000 Hz for bone conduction pathways, using the modified Hughson–Westlake Method as per recommended by ANSI 1997
^27^. Pure-tone audiometry is considered normal when the hearing thresholds at all frequencies are below 20 decibels hearing level (dBHL). Hearing loss will be classified according to the type and degree
^28^. The class of hearing loss in both ears will be assessed as normal hearing threshold (<20 dB), mild hearing loss (20 – 40 dB), moderate hearing loss (41 – 70 dB), severe hearing loss (70 – 90 db), and profound hearing loss (> 90 db). The hearing class is determined as the average of threshold in 250 Hz, 1000, 2000, and 4000 Hz. The possible interactions of the aforementioned variables and the amount of each primary or secondary outcome will be studied.

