## Statistical assessments

All statistical tests will be performed using
SPSS (V20.0, IBM Corporation, New York, USA). To determine whether the anodal, cathodal, and sham tDCS groups are well-matched in terms of age, sex, quality of tinnitus, tinnitus laterality, THI score, and duration and class of hearing loss, these dependent variables will be compared between the three groups using independent samples t-tests.

For nominal data like gender and class of hearing loss, Chi-square tests will be conducted across groups. Independent sample t-tests were also used to determine if individual baseline measures differed between groups (THI, tinnitus loudness, and distress). Prior to conducting
*t*-tests, Levene’s test for equality of variances was used. In no instance was Levene’s test violated; thus, equality of variances was assumed. The number of female and male participants and the quality of tinnitus symptoms, across each group will be compared using Pearson Chi-square tests. Mixed repeated-measure ANOVAs with the within‐subject factor time and the between‐subject factor stimulation were performed for evaluating changes in THI, tinnitus loudness, tinnitus distress, BDI and BAI scores. For the ANOVAs, sphericity was tested with the Mauchly’s test, and in the event of a violation of Mauchly’s test, the Greenhouse-Geisser correction was applied. In case of significant effects, follow-up post-hoc t-tests were carried out using LSD adjustments for multiple comparisons to examine if tDCS caused a significant difference relative to sham or baseline. An analysis of covariance will be performed with Time as within-subject factor, Stimulation as between-subject factor, and gender, laterality of tinnitus, duration of tinnitus as covariates. In addition, we will calculate Pearson’s correlations between change of THI and tinnitus loudness and distress values from pre- to post-stimulation.

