## Discussion

Recent studies have shown beneficial effects of tDCS in improving cognitive functions in healthy individuals
^7^ and also symptoms of different neuropsychiatric disorders such as depression
^8^, obsessive compulsive disorder
^9^, auditory-verbal hallucinations
^10^, and chronic pain
^11^. The therapeutic effects of tDCS in tinnitus have been reported by several studies; however, the findings are heterogeneous and controversial. In addition, most of the conducted studies have focused on single session tDCS, with short follow-up periods ranging some hours, to a few days
^13,
16,
33^. The present study aims to investigate the therapeutic efficacies of repeated sessions of bilateral tDCS (anodal/cathodal over the left/right AC) on tinnitus symptoms, its loudness, and distress in patients with intractable chronic tinnitus. The main advantage of this study is that it is a double blinded which will remove the placebo effects of the tDCS. The other main advantage of this study is the one month follow-up which is relatively long period, compared to the previous studies. Moreover, we aim to evaluate the possible interactions between the disease specific features and treatment response to develop a more specific and disease oriented tDCS protocol. To our knowledge this will be the first study of repeated sessions of tDCS with one month follow-up. Considering the repeated sessions of tDCS in this study, we will investigate the AEs of and tolerability of the patients in this study.

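### The protocol aims to learn which tinnitus features go with response to tDCS, but no stated analysis contains a Stimulation x feature term, and hearing-loss class, tinnitus type and baseline THI are missing from the only model with patient features

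*Protocol article*

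**What the plan says.** The aim appears in four places in the protocol article.

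- Abstract: "the possible interactions between the disease specific features including the hearing loss, laterality, type of tinnitus, and treatment response will be evaluated".
- Background: an association with treatment response is to be evaluated for "gender, THI basal score, laterality, tinnitus quality, duration, hearing loss class, etc".
- Hearing assessment: "The possible interactions of the aforementioned variables and the amount of each primary or secondary outcome will be studied".
- Discussion: the purpose is to "evaluate the possible interactions between the disease specific features and treatment response to develop a more specific and disease oriented tDCS protocol".

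In Statistical assessments, one outcome model contains patient features: an analysis of covariance with Time as the within-subject factor, "Stimulation as between-subject factor, and gender, laterality of tinnitus, duration of tinnitus as covariates". No interaction between Stimulation and a feature is stated there or elsewhere.

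In that section the other features appear only in checks of baseline balance. For hearing loss: "For nominal data like gender and class of hearing loss, Chi-square tests will be conducted across groups". For tinnitus type: "the quality of tinnitus symptoms, across each group will be compared using Pearson Chi-square tests". Baseline THI is likewise compared between groups at baseline.

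**The concern.** Two questions are easily confused. The prognostic question is who improves, whatever they receive. The effect-modification question is for whom active stimulation does better than sham. A stimulation protocol fitted to the disease needs an answer to the second.

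A covariate with no Stimulation x feature term addresses only the first. If, for example, patients with shorter duration improve more in all three arms, duration will look like a predictor of response although it says nothing about the benefit of tDCS over sham. With only the stated model to hand, a significant covariate is likely to be reported as a predictor of tDCS response. Hearing loss and tinnitus type, two of the three features that the Abstract names, would not be examined against outcome at all.

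**Working it through.** **1. Features in the aims against features in the analysis.**

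| Feature | Named in | Use in Statistical assessments |
|---|---|---|
| Hearing loss (class) | Abstract, Background, Hearing assessment | Baseline comparison only |
| Type or quality of tinnitus | Abstract, Background | Baseline comparison only |
| Laterality | Abstract, Background | Baseline comparison; covariate |
| Baseline THI | Background | Baseline comparison only, as a feature |
| Gender | Background | Baseline comparison; covariate |
| Duration | Background | Covariate |

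The other analyses do not fill the gap. The correlations are "Pearson’s correlations between change of THI and tinnitus loudness and distress values from pre- to post-stimulation" and involve no patient feature. The responder chi-square tests compare the three conditions and involve none either.

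**2. What the stated model can estimate.** With Time, Stimulation and a covariate, a repeated-measures analysis of covariance can give the covariate effect and covariate x Time. Both average over anodal, cathodal and sham. Whether the stimulation effect on change differs by feature is the Stimulation x Time x feature term (or Stimulation x feature, if the outcome is the post-intervention score). That term is not in the model.

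**3. Simulated illustration.** 4,000 trials, 30 per arm, one outcome with SD 1, a 50:50 feature, and one active arm having an effect of 0.903 SD in one level of the feature only. The covariate effect was significant in 27% of runs, a result that cannot be told apart from a prognostic effect common to all arms. The Stimulation x feature test (2 degrees of freedom) was significant in 41%.

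**4. How much precision to expect.** Inputs from Sample size calculation: 85% power, 95% confidence, 22 patients, raised to 25 in each group. The Abstract gives n=90, which is 30 per arm at 1:1:1, so both sizes are used. The means and SDs for Equation 1 are not given, so 22 cannot be reproduced. It can only be solved backwards, reading it as per group:

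- d = (1.960 + 1.036) x sqrt(2/22) = 0.903 SD.

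For one active arm against sham and a two-level feature with share s:

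- SE of the interaction = sqrt((2/n) x (1/s + 1/(1 - s))), in SD units.
- Power = Phi(d/SE - 1.960), for an interaction as large as d.

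| n per arm | Split | SE | Power |
|---|---|---|---|
| 25 | 50:50 | 0.566 | 36% |
| 30 | 50:50 | 0.516 | 42% |
| 25 | 20:80 | 0.707 | 25% |
| 30 | 20:80 | 0.645 | 29% |

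At 50:50 the SE is twice that of the treatment effect, sqrt(2/n). For an interaction of d/2 at 50:50, power is 12% to 14%. If 22 were instead the total of two groups, d would be 1.278 SD. Power for an interaction that large, at 50:50, would be Phi(1.278/0.566 - 1.960) = 62% at 25 per arm and Phi(1.278/0.516 - 1.960) = 70% at 30. The per-group reading is the natural one, since the next sentence of the protocol speaks of 25 in each group.

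**The case against.** The strongest reply is that the protocol never says this analysis of covariance serves the interaction aim. It may simply be a covariate-adjusted version of the mixed ANOVA described before it, with the method for an exploratory question left to a fuller document. The first half of this stands: a reader might infer that the protocol assigns that model to the aim, and no sentence does so. The second half does not dispose of the point. The article sets out its model and covariate list, and if these are followed, no stated analysis addresses effect modification.

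A second reply is that the aim is looser than effect modification. The Background speaks of association, the Hearing assessment section relates features to the amount of the outcome, and response is defined as a within-patient fall of at least 20 THI points. On that reading covariate x Time terms do bear on gender, laterality and duration. That is fair, and so it would be too strong to say that the model has main effects only. But the Abstract speaks of interactions, the Discussion gives a purpose that needs a comparison with sham, and hearing loss, tinnitus type and baseline THI are left out on either reading.

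Two further inferences are not supported. One is that laterality is wrongly entered because it has three unordered levels: the protocol does not list its levels, and a two-level coding would be harmless. The other is that 0.90 SD is the planned effect: it is solved backwards and appears nowhere in the protocol.

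**Conclusion.** The concern holds in this form: the protocol promises to evaluate how disease features interact with treatment response, and no stated analysis can show whether the tDCS-versus-sham difference varies with a feature. Two of the three features named in the Abstract, and baseline THI from the Background, are not in the only model with patient features. This rests on the text alone.

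The consequence is limited to this exploratory aim. The randomised comparisons of THI, loudness, distress and responders are untouched. The power figures are illustrative: they depend on reading 22 as per group, on an assumed split of the feature, on one active arm against sham, and on an interaction as large as the implied effect. They support only the exploratory label and apply equally to the corrected analysis.

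**What to change.** For each named feature, one at a time, add Stimulation x feature (x Time) terms to the THI model, using the planned post-intervention assessments (immediately after the last session and at one month). The protocol does not put one of these above the other, so both should be covered. For baseline THI as the feature, use the post-intervention scores as outcome, so that the pre-intervention score is not both a response and a modifier.

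Enter any feature with more than two unordered levels as a factor, and group sparse levels before the data are seen. Baseline evaluations lists nine categories of tinnitus type, which at 25 per arm averages 25/9 = 2.8 patients per category per arm (30/9 = 3.3 at 30). Report interaction estimates with 95% confidence intervals, labelled exploratory, and do not present covariate or covariate x Time effects as evidence of who benefits from tDCS.

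The alternative is to restate the aim as prognostic association, and then to add the missing features to the model or remove them from the aim.

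The cost is a few extra models on data already to be collected. The drawbacks are wide intervals and several unadjusted tests, so the results can only generate hypotheses.

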## Sample size calculation

The sample size of this study was calculated using the standard sample size formula (represented in
Equation 1). The study of Shakhawat
*et al.* was considered as the basic study to determine the sample size of our study with the predetermined power and level of significance. Considering the power of 85 percent and for confidence interval of 95 percent, the sample size of this study is 22 patients. We will use 25 patients in each group so that future attrition of the patients due to long term period of the tDCS sessions will be compromised.

$$n=\frac{{\left(z_{1–\frac{\alpha }{2}}+z_{1–\beta }\right)}^{2}(S_{1}^{2}+S_{2}^{2})}{{\left({\bar{X}}_{1}-{\bar{X}}_{2}\right)}^{2}}\;Equation\;1$$

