## Methods/design

### Participants

This is a part of a larger project which is designed to comprehensively investigate the efficacy of different tDCS protocols at different sites of brain for treatment of intractable chronic tinnitus. In this double blinded placebo controlled randomized trial will be conducted on intractable tinnitus patients (n=90) who will be randomly divided into three groups of anodal (anode/cathode on left/right AC), cathodal (cathode/anode on left/right AC, and sham (anode/cathode on left/right AC) tDCS. In the sham treatment, after 30 sec the device will be turned off without informing the patients. The experimental procedures of the study including tDCS interventions and the evaluations of the outcomes will be performed in the Bioelectromagnetic Clinic in Ahvaz Imam Hospital, Ahvaz, Iran. Patients with intractable chronic tinnitus (> 2 years) will be enrolled in this study. This is a single-center, non-stratified, with balanced randomization [1:1:1], double-blind, placebo-controlled, parallel-group study conducted in Bioelectromagnetic Clinic, Imam Khomeini Hospital, Ahvaz, Iran. Allocation concealment will be performed by random allocation cards using computer-generated random numbers. The patients will be randomly assigned into three groups of cathodal, anodal, or placebo tDCS.

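### The protocol gives two trial sizes (90 and 75) and does not say which comparison of the three-arm analysis its 85% power covers; the calculated 22 completers per arm fall short of it under the planned analysis

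*Protocol article*

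**What the plan says.** Two sections give the total as 90. The Abstract describes "patients (n=90) with intractable chronic tinnitus" divided into three groups. Methods/design, Participants says the "trial will be conducted on intractable tinnitus patients (n=90) who will be randomly divided into three groups", and fixes the allocation at 1:1:1.

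The Sample size calculation section takes one earlier study as its basis, with 85% power and 95% confidence. It concludes that "the sample size of this study is 22 patients", and then says: "We will use 25 patients in each group so that future attrition of the patients" is allowed for. Equation 1, given there, contains two means, two variances and a two-sided alpha. The section does not give the outcome, means, SDs or a dropout rate.

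The Statistical assessments section plans mixed repeated-measures ANOVAs over the three stimulation groups. Where an effect is significant, post-hoc t-tests with LSD follow, to compare tDCS with sham or with baseline. Every test uses P < 0.05. The Trial status section says that patients have been enrolled and that allocation is still to come.

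**The concern.** The document makes two current statements about its own size, and they cannot both be true. The allocation list has to be generated for one total, and the attrition the trial can absorb depends on which total is meant.

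The second part concerns what the 85% means. Equation 1 sizes a single comparison of two groups. The trial has three arms and at least two comparisons of interest, anodal versus sham and cathodal versus sham, reached through an omnibus test. The 85% could refer to one pairwise comparison, to each of two, or to showing both active arms better than sham. These have different powers at the same sample size, and a reader cannot tell which is claimed.

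**Working it through.** **Trial size.** Abstract and Participants: 90 / 3 = 30 per arm. Sample size calculation: 3 × 25 = 75. Difference: 90 − 75 = 15 patients, or 5 per arm.

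**Attrition allowance over 22.** With 25 per arm: 1 − 22/25 = 12%. With 30 per arm: 1 − 22/30 = 26.7%. The document states no rate.

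**The plan's figure of 22.** It cannot be reproduced forwards, because the means and SDs are not given. It can be solved backwards. With equal variances, Equation 1 is n = 2(z₁₋α/₂ + z₁₋β)² / d². For two-sided 0.05 and 85% power the quantiles are 1.960 and 1.036. If 22 is per group, d = (1.960 + 1.036) × √(2/22) = 0.903. If 22 was rounded up from just above 21, d could be as large as 0.925. If 22 were the total of two groups (11 each), d would be 1.28. The per-group reading is inferred from the next sentence, which speaks of 25 in each group. All results below assume it, with d = 0.903.

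**One unadjusted pairwise comparison, as in Equation 1.** Power ≈ Φ(d√(n/2) − 1.960).
- n = 22: Φ(2.996 − 1.960) = 85.0%
- n = 25: Φ(3.194 − 1.960) = 89.1%
- n = 30: Φ(3.499 − 1.960) = 93.8%

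A two-sample t-test in place of the normal approximation gives 83%, 88% and 93%.

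**The planned sequence.** This was simulated as a one-way version on a single endpoint: a three-group F-test at 0.05 and, if significant, LSD t-tests at 0.05 using the pooled variance. Each setting had 100,000 runs, and a repeat with 1,000,000 runs agreed to within half a percentage point. Both active arms differ from sham by d = 0.903.

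| Evaluable per arm | One given active arm vs sham | Both active arms vs sham |
|---|---|---|
| 22 | 80% | 74% |
| 25 | 86% | 80% |
| 27 | 88% | 84% |
| 30 | 92% | 88% |

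If only one active arm has the effect, its power is the same to within rounding (80%, 86% and 92% at 22, 25 and 30). With no effect in any arm, the chance of at least one false active-versus-sham claim is about 4% with the F-test gate and about 9% without it.

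**The case against.** A reader might infer that a three-arm trial sized with a two-group formula does not have 85% power. The documents do not support that as a general statement. Sizing each pairwise comparison with a two-group formula is common, and at 22 per group Equation 1 returns its 85% for one comparison at 0.05. The gap between that and 83% is only the normal approximation against the t-test.

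A reader might also test each active arm at 0.025. By the t-test that gives about 75%, 81% and 88% at 22, 25 and 30 per arm. The protocol plans no such split. It plans an omnibus test and then LSD, and with three groups and one endpoint that sequence already limits the family-wise error. Even with the split, 30 per arm exceeds 85%.

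A third objection is that every power figure rests on a back-solved effect. The inputs come from a study not at hand, and leaving means and SDs out of an article may be condensation. This is fair, and it is why the figures here are illustrative and should not be copied into the protocol. If 22 were a two-group total, d would be 1.28 and power at 22 or more per arm would be far above 85%.

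Finally, enrolment is reported as done, so the authors already know how many patients they have. That makes the correction easy, but it does not tell the reader which number is right.

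None of this touches the conflict between 90 and 75. What also stands is that the section does not say which comparison the 85% covers, and that the planned sequence misses 85% at exactly the 22 completers on which the claim is built.

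**Conclusion.** The contradiction in trial size is certain and needs correcting: 90 (30 per arm) against 75 (25 per arm), with an attrition allowance of 27% or 12% accordingly.

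The power point holds in a limited form. Under the planned sequence, 22 evaluable per arm falls about 5 points short of 85% per active-versus-sham comparison. At 25 or more evaluable the target is met per comparison. If the aim is to show both active arms better than sham, 22, 25 and 27 evaluable all fall short, and 30 does not.

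These figures assume that 22 is per group, that d is about 0.90 in each active arm, and that a one-way comparison stands in for the mixed ANOVA. With d = 0.925 the per-comparison power at 22 is about 82%, so the conclusion is unchanged. It might be tempting to conclude that 90 must be the intended total because it supports the power claim. The documents do not show which total is meant, and only the authors can settle it.

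**What to change.** Before allocation:

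1. State the one true total and per-arm number in the Abstract, Participants and Sample size calculation sections, with the attrition allowance that follows from it.
2. State whether 22 is per group, as the text implies, and which outcome, means and SDs produced it.
3. State which comparison the 85% refers to: one active arm against sham, each of the two, or both together.
4. Restate the power for the three-arm analysis at the expected number of completers, using the authors' own means and SDs and not the back-solved effect used here.

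This is a correction of text plus one short recalculation. It needs no patients beyond those already stated. The only downside is that the stated power may come out slightly lower than 85%, depending on the number of completers and the comparison chosen.
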